## Substudy 4. Epidemiological prevalence study

### Objective/s

Determine the prevalence of SARS\_COV2 infection in Spanish pregnant women

### Design

Cross-sectional study.

The nQuery Advisor Release 7.0 software was used to calculate the sample size, based on the available data. As we do not have data on the prevalence of COVID-19, we set an expected percentage of 50% (a situation that maximizes the sample size) of asymptomatic women during delivery. We determined the sample size for a COVID-19 delivery prevalence study with an expected prevalence of 50%, a 95% confidence level and 5% accuracy, resulting in a sample size of 1056 pregnant women.

The selection of pregnant women in the sample will follow the distribution of the delivery rate by communities and hospitals in Spain according to the INE data for 2018 (Appendix 3) (15). Subsequently, a simple random selection procedure will be carried out in each site, creating a numerical list of the women to be included in the sample (Appendix 1). Pregnant women will be assigned a consecutive number from one onwards according to their due date. Subsequently, the pregnant women who will be part of the sample will be chosen when the number that identifies them is within the table previously created through the random procedure.

Recruitment: 1st March 2020 to 1st March 2021. Spanish sites collected in the Appendix 1

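### The Substudy 4 sample size of 1056 cannot be reproduced from its stated inputs, which give 385; either the 5% accuracy or an unstated adjustment needs correcting

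*Protocol*

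**What the plan says.** Protocol, Substudy 4, Design, gives a completed calculation. On the software it says "The nQuery Advisor Release 7.0 software was used to calculate the sample size, based on the available data". Because prevalence is unknown, "we set an expected percentage of 50% (a situation that maximizes the sample size) of asymptomatic women during delivery". The next sentence gives the result for a study of COVID-19 prevalence at delivery: "with an expected prevalence of 50%, a 95% confidence level and 5% accuracy, resulting in a sample size of 1056 pregnant women".

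The same section describes the sampling. Numbers are allocated to communities and hospitals in proportion to births, and then "a simple random selection procedure will be carried out in each site". It mentions no design effect, non-response allowance, finite population correction, power or subgroup target.

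Appendix 3 spreads a total of 1056 tests over 52 provincial rows in proportion to 370,827 births. No other sample size is calculated in the protocol: Study population and selection criteria says that none was made for the clinical-course description, and Overall sample size gives only 100 sites and 172,000 deliveries.

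**The concern.** The inputs and the result stand in one sentence and do not agree. Prevalence estimation is the sole objective of Substudy 4, and this is the protocol's only quantitative sizing. A reader cannot tell whether 1056 women were meant to deliver ±5 points, ±3 points or something between, because that depends on an adjustment that is not shown.

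A smaller inconsistency sits beside it. One sentence attaches the 50% to asymptomatic women and the next to COVID-19 prevalence, so the quantity being sized is not named consistently.

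**Working it through.** **Inputs (Protocol, Substudy 4, Design).** p = 0.50; 95% confidence, taken as two-sided, z = 1.96; accuracy 5%, taken as an absolute half-width d = 0.05; stated result 1056.

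**Step 1: the plan's own calculation.**
n = z² p(1 − p) / d² = 3.8416 × 0.25 / 0.0025 = 384.2, so 385. The stated figure is 1056 / 384.2 = 2.75 times larger.

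**Step 2: variants that keep p = 50% and 5%.**

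| Variant | n |
|---|---|
| One-sided 95% | 271 |
| Wilson interval | 381 |
| Finite population correction, 172,000 or 370,827 | 384 |
| Clopper-Pearson interval | 402 |
| Continuity-corrected | 404 |
| 99% confidence (changes the stated level) | 664 |
| 5% read as total width (d = 0.025) | 1537 |
| 385 inflated for 5% to 50% loss | 406 to 770 |

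None is close to 1056. A different prevalence cannot close the gap either, since p(1 − p) is largest at 50%, as the protocol itself notes.

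**Step 3: what would give about 1056.** Each of these changes or adds an input.
- Half-width 3 points: 3.8416 × 0.25 / 0.0009 = 1067.1, so 1068. With a finite population of 172,000 this is 1061. With a population of 100,000, a figure that the protocol does not give, it is 1055.9, so 1056.
- Design effect on 385: 1056 / 385 = 2.74.
- Loss or non-response from 1056: 1 − 385 / 1056 = 64%.
- 99.9% confidence with ±5 points: 1083.
- 90% confidence with a total width of 5 points: 1083.
- One-sample test of 50% against 55% with 90% power: 1047 to 1051.

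**Step 4: precision of 1056 women at 50%.** Half-width = 1.96 × √(DE × 0.25 / 1056), where DE is the design effect. The values of DE are assumptions, as the protocol states none.

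| DE | Half-width, points |
|---|---|
| 1 (simple random sampling) | 3.02 |
| 1.5 | 3.7 |
| 2 | 4.3 |
| 2.75 | 5.0 |

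**Step 5: precision at lower prevalences.** The prevalences are assumptions, with simple random sampling and n = 1056.

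| Prevalence | Expected cases | Half-width, points |
|---|---|---|
| 1% | 11 | 0.60 |
| 3% | 32 | 1.03 |
| 5% | 53 | 1.31 |
| 10% | 106 | 1.81 |

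At the low end the symmetric form is rough: for 11 of 1056 the exact 95% interval is 0.52% to 1.86%.

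**Step 6: is 1056 a typing slip?** No. The 52 rows of Appendix 3 sum to 370,827 births and 1056.04 tests, so 1056 was carried through.

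**The case against.** The best defence is that the precision may be right and only the derivation incomplete. Women are drawn from many sites under an allocation by community and hospital, the option chosen in the software is not given, and a design effect near 2.75 would restore ±5 points exactly. This stands. A reader might infer that the 5% is a slip for 3%, since ±3 points lands near 1056. That is the simplest reading, but the protocol does not say so, and the exact match needs a population size that is not in it. What the defence does not rescue is the text: an adjustment that nearly triples the sample has to be stated.

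The second objection is that nothing is lost, and as to enrolment that is right. A reader might infer that a sizing error means an undersized study. Under simple random sampling 1056 is more than the ±5 points require. Nor does the possibility of low prevalence make matters worse: at assumed prevalences of 1% to 10% the half-width is 0.6 to 1.8 points.

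Third, the mention of asymptomatic women might suggest that the target is the asymptomatic share of infected women, which would require counting infected women and not deliveries. The documents do not support that. The Substudy 4 objective is prevalence, the sizing sentence opens with the lack of prevalence data, and the next sentence names a prevalence study. This is a wording fault.

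**Conclusion.** The sample size is not reproducible from the inputs given: 385 against 1056, a factor of 2.75. This rests on a two-sided 95% level and on 5% as an absolute half-width; the one-sided and total-width readings do not give 1056 either.

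The documents do not settle which part is wrong. If no adjustment was made, the stated 5% misdescribes 1056 women, whose half-width at 50% is about 3.0 points under simple random sampling. If an adjustment of about 2.75-fold was made, the 5% may stand and the adjustment is missing.

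This is an error of reporting and justification in the safe direction. It changes no enrolment, allocation or analysis. It should be fixed, but it is not a condition for the substudy to go ahead.

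**What to change.** Keep 1056 and correct the sizing paragraph in Substudy 4, Design. The sponsor first establishes how 1056 was obtained.

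- **If no adjustment was applied**, replace the 5% statement with: *Under simple random sampling, 1056 women give a 95% confidence interval half-width of about 3.0 percentage points at 50% prevalence, and about 0.6 to 1.8 points at assumed prevalences of 1% to 10%; exact intervals will be used at the low end.*
- **If a design effect or non-response allowance was applied**, state its value and the precision that results.
- **In either case**, attach the 50% to one target: the prevalence of PCR-positive women at delivery among women without a positive test before delivery, as the Substudy 4 inclusion criteria require. Remove the reference to asymptomatic women from the sizing sentence.

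The cost is one paragraph. Appendix 3 and the number of women stay as they are.

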## Overall sample size

Currently, the percentage of pregnant patients who are being diagnosed with COVID-19 is unknown, this being one of the objectives of the study. The registry includes 100 sites that in 2019 cared for a total of 172,000 deliveries (Appendix 1 and 3).

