## Statistics

For the statistical analysis, the SAS v9.4 software will be used.

The set of groups of variables requested and collected for each enrolled patient will be the same. The demographic and clinical characteristics of the population included will be summarized. Mean, standard deviation, minimum and maximum or median and interquartile intervals will be used for continuous variables, according to the distribution. The corresponding absolute and relative frequency will be reported for the discrete variables.

The possible association of both the characteristics of the patients and the *outcomes* collected with COVID-19 infection using the Pearson Chi-square test or Fisher's exact test and the Mann-Whitney U test (after checking the absence of normal data using the Kolmogorov-Smirnov test). Statistically significant associations were considered when the p value was less than 0.05. For those categorical variables in which statistically significant differences were identified, the corresponding Odds Ratio (OR) and 95% Confidence Intervals (95% CI) were estimated using univariate logistic regression models.

Logistic regressions, both univariate and multivariate, will be performed, determining the odd ratio and its 95% confidence interval.

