### FORMS

Baseline form

History Form

COVID19 diagnosis

Ward/ICU admission

Pregnancy follow-up 12 weeks

Pregnancy follow-up 20 weeks

Pregnancy follow-up 35 weeks

Gestational control

Emergency visit

Delivery form

Basic new-born form

Second twin form

Lab tests

Blood type

Anaesthesia

End Form

---

Appendix 3: Case distribution according to Spanish provinces (INE 2018): data adapted to the study.

| 7  |                           | Total nacimientos | %     |   | Total test | %     |
|----|---------------------------|-------------------|-------|---|------------|-------|
| 8  | Total                     | 370.827           | 100   |   | 1056       | 100   |
| 9  | 02 Albacete               | 3.040             | 0,82  | ✓ | 8,66       | 0,82  |
| 10 | 03 Alicante/Alacant       | 14.161            | 3,82  | ✓ | 40,33      | 3,82  |
| 11 | 04 Almería                | 7.417             | 2,00  | ✓ | 21,12      | 2,00  |
| 12 | 01 Araba/Álava            | 2.683             | 0,72  | ✓ | 7,64       | 0,72  |
| 13 | 33 Asturias               | 5.733             | 1,55  | ✓ | 16,33      | 1,55  |
| 14 | 05 Ávila                  | 979               | 0,26  | ✓ | 2,79       | 0,26  |
| 15 | 06 Badajoz                | 5.210             | 1,40  | ✓ | 14,84      | 1,40  |
| 16 | 07 Balears, Illes         | 10.285            | 2,77  | ✓ | 29,29      | 2,77  |
| 17 | 08 Barcelona              | 46.687            | 12,59 | ✓ | 132,95     | 12,59 |
| 18 | 48 Bizkaia                | 7.945             | 2,14  | ✓ | 22,62      | 2,14  |
| 19 | 09 Burgos                 | 2.351             | 0,63  | ✓ | 6,69       | 0,63  |
| 20 | 10 Cáceres                | 2.611             | 0,70  | ✓ | 7,44       | 0,70  |
| 21 | 11 Cádiz                  | 10.246            | 2,76  | ✓ | 29,18      | 2,76  |
| 22 | 39 Cantabria              | 3.805             | 1,03  | ✓ | 10,84      | 1,03  |
| 23 | 12 Castellón/Castelló     | 4.580             | 1,24  | ✓ | 13,04      | 1,24  |
| 24 | 13 Ciudad Real            | 3.676             | 0,99  | ✓ | 10,47      | 0,99  |
| 25 | 14 Córdoba                | 6.209             | 1,67  | ✓ | 17,68      | 1,67  |
| 26 | 15 Coruña, A              | 7.132             | 1,92  | ✓ | 20,31      | 1,92  |
| 27 | 16 Cuenca                 | 1.303             | 0,35  | ✓ | 3,71       | 0,35  |
| 28 | 20 Gipuzkoa               | 5.472             | 1,48  | ✓ | 15,58      | 1,48  |

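### Substudy 4 draws women within sites under province quotas, but its stated analysis uses no weights and ignores hospitals, so a national prevalence may be shifted and its interval too narrow

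*Protocol*

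**What the plan says.** The only objective of Substudy 4 is the prevalence of infection in Spanish pregnant women. Its Design section fixes the sampling in two steps. First, "The selection of pregnant women in the sample will follow the distribution of the delivery rate by communities and hospitals in Spain"; Appendix 3 ("Case distribution according to Spanish provinces (INE 2018): data adapted to the study") turns this into quotas for 52 provinces. Second, "a simple random selection procedure will be carried out in each site", and a woman enters only if her consecutive number is on the list drawn beforehand. The size is justified by "an expected prevalence of 50%, a 95% confidence level and 5% accuracy, resulting in a sample size of 1056 pregnant women". No design effect or intra-hospital correlation is named.

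The Statistics section of Substudy 4 says "The corresponding absolute and relative frequency will be reported for the discrete variables". It compares groups "using the Pearson Chi-square test", Fisher's exact test or the Mann-Whitney test. Odds ratios for significant categorical variables "were estimated using univariate logistic regression models", and multivariate logistic models follow. No weight, stratum or hospital term is mentioned, and no interval method for the prevalence is named.

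The registry-wide section Heterogeneity tests plans Q or I² statistics, meta-regression and random intercepts for centre. It ties the intercepts to regression models described above it, but no model stands above it. The Substudy 4 Statistics section does not refer back to it.

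On coverage, the section Overall sample size says "The registry includes 100 sites that in 2019 cared for a total of 172,000 deliveries". Appendix 3 gives 370,827 births for 2018.

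**The concern.** The design takes trouble to mirror the geography of births, and the stated analysis then treats the women as one simple random sample. Two things are at stake for the substudy's only objective.

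- **The estimate.** An unweighted proportion reproduces the birth-proportional mix only if the quotas are met. The protocol gives reasons to expect gaps. Entry needs consent and a PCR within 72 hours before or 24 hours after delivery (Inclusion criteria). No extra tests are done and each site follows its own testing protocol (Safety Measures and Confidentiality). Informing the patient is left to the doctor (Patient referral sources). Substudy 3 is set in hospitals with universal screening; Substudy 4 carries no such condition.
- **The uncertainty.** Women delivering in one hospital share a catchment and a local epidemic curve. If the result is read as a figure for Spain, variation between hospitals belongs in the interval, and a binomial formula leaves it out.

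**Working it through.** **Inputs from the protocol.** N = 1056, expected proportion 0.50, 95% confidence, accuracy 5 points (Substudy 4, Design); 100 sites and 172,000 deliveries (Overall sample size); province births and quotas (Appendix 3).

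**Assumptions, not in the protocol.** Intra-hospital correlation (ICC) 0.01 to 0.05; coefficient of variation (CV) of site size 0 or 0.9; all 100 sites take part; the province prevalences in step 3.

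**1. The plan's own size.** n = z²p(1−p)/d² = 1.96² × 0.25 / 0.05² = 384.1, so 385. The stated 1056 is not reproduced. It is 1056/384.1 = 2.75 times what these inputs need. Under simple random sampling its half-width is 1.96 × √(0.25/1056) = 3.02 points.

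**2. The allocation.** The 52 rows add to 370,827 births and 1056.04 women. No quota differs from exact proportionality by more than 0.005 women, so the design is self-weighting by province if the quotas are met. Eleven provinces are allotted fewer than 5 women (for example Soria 1.73, Zamora 2.55). Madrid and Barcelona together hold 15.52% + 12.59% = 28.1%.

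**3. Missed quotas.** Suppose Madrid (share 0.1552) fills its quota and all other provinces reach half of theirs, with prevalence 5% in Madrid and 1% elsewhere.

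- True value: 0.1552 × 5% + 0.8448 × 1% = 1.62%.
- Madrid's share of the realised sample: 0.1552 / (0.1552 + 0.8448/2) = 0.2687.
- Unweighted value: 0.2687 × 5% + 0.7313 × 1% = 2.07%, which is 28% too high in relative terms.
- If the other provinces reach 80% of quota instead, Madrid's share is 0.1868 and the unweighted value 1.75%.
- Variance cost of reweighting in the first case (Kish factor): 0.1552²/0.2687 + 0.8448²/0.7313 = 1.07.

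**4. Clustering, for inference beyond the participating sites.** Mean women per site m = 1056/100 = 10.56. Design effect = 1 + ((1 + CV²)m − 1) × ICC. True coverage of a nominal 95% interval that ignores it = 2Φ(1.96/√deff) − 1. Half-width with the design effect = 3.02 × √deff points at p = 0.5.

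| Site-size CV | ICC | Design effect | Coverage | Half-width, p = 0.5 |
|---|---|---|---|---|
| 0 | 0.01 | 1.10 | 93.9% | 3.16 |
| 0 | 0.02 | 1.19 | 92.8% | 3.29 |
| 0 | 0.05 | 1.48 | 89.3% | 3.67 |
| 0.9 | 0.01 | 1.18 | 92.9% | 3.28 |
| 0.9 | 0.02 | 1.36 | 90.7% | 3.52 |
| 0.9 | 0.05 | 1.91 | 84.4% | 4.16 |

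**5. Is the stated accuracy lost?** No. Every half-width in the table is below 5 points. The 5% holds up to a design effect of 2.75, that is, an ICC of (2.75 − 1)/(10.56 − 1) = 0.18 with equal sites, or (2.75 − 1)/(1.81 × 10.56 − 1) = 0.097 with CV 0.9.

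**6. Coverage of the country.** 172,000/370,827 = 46%, comparing 2019 deliveries with 2018 births. No random selection of sites is described.

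**The case against.** The strongest reply is that hospitals are not sampled at all. If the target is deliveries at the participating sites, every site enters with certainty and the hospitals act as strata. With roughly proportional allocation the variance is then at or slightly below that of simple random sampling, and the under-coverage in the table disappears. This is correct, and it limits the point. But the stated target is Spanish pregnant women, and for that target variation between hospitals counts.

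A second reply is that the pre-drawn list prevents a site from over-enrolling. That also stands. Imbalance does not need over-enrolment, though: shortfalls through refusal or missing tests have the same effect, and the illustration uses shortfalls only.

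A third is that weights and interval methods may be left to a statistical analysis plan, and that centre random intercepts are already foreseen. In part this stands: the protocol names no prevalence interval, and the logistic models could be brought under the registry-wide provision. But the protocol does name the summary and the tests, and these do not match its own sampling. The intercepts cover neither the prevalence nor the two-group tests.

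Stronger readings that a reader might infer are not supported:

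- *The sample is too small because clustering was ignored.* The stated inputs need only 385 women, so 1056 leaves ample room.
- *All p-values are too small.* That is secure for characteristics shared by a whole hospital if the ICC is positive. For characteristics that vary within hospitals the error can go either way.
- *The unweighted prevalence is biased as planned.* The allocation is exactly proportional; the shift needs both missed quotas and differing prevalence.
- *Weighting would make the result nationally representative.* It cannot repair non-random selection of sites.

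**Conclusion.** The point holds in a conditional form and is worth correcting. The stated analysis of Substudy 4 ignores the sampling that the same substudy prescribes. The unweighted prevalence moves if quotas are missed and prevalence differs by province: 2.07% against 1.62% in the illustration, 1.75% with a milder shortfall. For national inference with positive between-hospital correlation, a simple binomial 95% interval covers about 94% to 84%. This second range rests on an assumed ICC of 0.01 to 0.05 and a site-size CV up to 0.9; the protocol gives neither. The planned sample and the stated 5% accuracy are not in danger. The site list was not available, so the number of hospitals per province could not be checked.

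**What to change.** Change the Statistics section of Substudy 4 as follows.

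1. Report the prevalence post-stratified to the Appendix 3 birth shares. Group provinces into autonomous communities or larger regions, so that each stratum holds enough women and at least two hospitals. With 52 provinces and 100 sites, under two per province on average, province strata with hospital clusters would fail wherever a province has one site.
2. Give a 95% confidence interval that allows for hospital clustering.
3. Use design-adjusted (survey) chi-square tests. For the logistic models use hospital as cluster, or refer explicitly to the centre random intercepts under Heterogeneity tests.
4. State that the estimate rests on participating sites that were not randomly selected, with 172,000 deliveries in 2019 (about 46% of the 370,827 births of 2018), and that weighting does not correct this.

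The cost is protocol or analysis-plan wording, slightly more analysis work with survey procedures in the same software, and a somewhat wider interval. No new data and no larger sample are needed.

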### Heterogeneity tests

Populations from diverse genetic, socio-cultural and socio-economic backgrounds can be quite different in their characteristics. Additionally, there may be some disparities between sites with respect to the quality and quantity of data items that each site can measure. This is expected regarding a data collection that allows any site to contribute. Consequently, heterogeneity in effect estimates may be due to clinical differences between pregnant women and/or site-level differences in terms of exposure and outcome determination (reporting or assessment bias). We will formally assess heterogeneity taking into account variations in exposure, covariates, and significant outcomes, and use meta-analysis methods (Q or I statistics, meta-regression, and subgroup analysis) to unravel heterogeneity at central and individual levels. Briefly, we will incorporate individual-level interaction terms in one-stage analysis and random intercepts to account for central-level factors not measured in the regression models mentioned above.

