### Inclusion criteria:

- Single or multiple gestations of 24 weeks or more without a positive laboratory test for COVID-19 prior to delivery.
- Delivery in a public or private maternity hospital in Spain with a diagnostic test for COVID-19 using PCR Kits within 72 hours prior to delivery or 24 hours after delivery.
- The presence of comorbidity is not an exclusion criterion (asthma, diabetes mellitus, hypertension-preeclampsia, endocrine disorder, dermatological pathology or other obstetric or medical-surgical pathologies).
- Acceptance by the pregnant woman to participate in the study by means of informed consent for group study.

The result of the PCR test on a sample of nasopharyngeal and/or oropharyngeal swab was considered synonymous with exposure/non-exposure, defining a case as any pregnant woman with a positive result, regardless of the symptoms. Those cases with clinical presentation of COVID-19 were classified according to the WHO division for adults into: mild symptoms, mild-moderate pneumonia, severe pneumonia and septic shock (16).

The recommended samples for diagnosis are samples from the upper respiratory tract: nasopharyngeal and/or oropharyngeal swab.

A healthy patient is considered to have a negative PCR in the absence of symptoms. Patients with positive IgM or IgG serology cannot be included. The absence of serology does not prevent classifying the patient as healthy if the PCR is negative.

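### Substudy 4 aims at prevalence in Spanish pregnant women but draws only within self-selected registry sites (about 46% of births), so the design does not by itself support a national figure

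*Protocol*

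**What the plan says.** - **Target.** The Objective/s section of Substudy 4 asks for the prevalence of "infection in Spanish pregnant women". The inclusion criteria are equally wide: "Delivery in a public or private maternity hospital in Spain", and the Patients section speaks of Spanish maternity wards in general.
- **Allocation.** The Design section of Substudy 4 says the selection "will follow the distribution of the delivery rate by communities and hospitals in Spain according to the INE data for 2018". Appendix 3 carries this out by province, against a total of 370,827 births and 1056 tests. Reference 15 shows that these births are counted by where the mother lives.
- **Draw.** The same Design section then says that "a simple random selection procedure will be carried out in each site", and gives the recruiting hospitals as "Spanish sites collected in the Appendix 1".
- **Sites.** Under Overall sample size: "The registry includes 100 sites that in 2019 cared for a total of 172,000 deliveries". The Heterogeneity tests section, on differences between sites in the data they can supply, adds: "This is expected regarding a data collection that allows any site to contribute". The protocol text reviewed describes no sampling of hospitals.

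**The concern.** The population named in the objective and used for the allocation is all deliveries in Spain. The population from which women can be drawn is deliveries at the registry sites. The text gives no route by which a woman delivering elsewhere could be selected.

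Random selection within a site makes the sample represent that site's eligible deliveries, and proportional quotas by province balance geography. Neither addresses which hospitals in a province joined a COVID-19 registry. If participating hospitals differ in infection prevalence from others in their province, a figure presented as national is biased. Taking more women at the same sites does not reduce that bias, and a binomial interval does not show it.

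At stake is what Substudy 4 may conclude: a prevalence for the participating hospitals, or one for Spain.

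**Working it through.** **Inputs from the protocol.** Births in 2018: 370,827 (Appendix 3). Deliveries at the 100 sites in 2019: 172,000 (Overall sample size). Substudy 4 sample: 1056 (Design).

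**1. The plan's own allocation.** Each row of Appendix 3 should equal 1056 × province births / 370,827. For Madrid, 1056 × 57,554 / 370,827 = 163.90, as printed. The 52 rows sum to 370,827 births and 1056.04 tests, and every row agrees with the formula to within 0.005. The allocation is therefore to all births in Spain, not to deliveries at the sites.

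**2. Coverage.** c = 172,000 / 370,827 = 0.464, leaving 0.536 outside the sites. This sets 2019 deliveries against 2018 births, so it is approximate. If births per delivery were 1.5% to 3% above one (assumption), c is 47.1% to 47.8%. If births in 2019 were 2% to 5% below 2018 (assumption), c is 47.3% to 48.8%. Coverage stays below one half in each case.

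**3. Relative bias.** Let r be prevalence at the sites divided by prevalence elsewhere. The documents give no value for r, so all of these are assumptions. The site-based figure divided by the true national figure is r / (c·r + 1 − c).

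| Assumed r | Site figure / national figure | Error in national figure |
|---|---|---|
| 0.5 | 0.5 / 0.768 = 0.65 | 35% too low |
| 0.67 | 0.667 / 0.845 = 0.79 | 21% too low |
| 0.8 | 0.8 / 0.907 = 0.88 | 12% too low |
| 1 | 1 | none |
| 1.25 | 1.25 / 1.116 = 1.12 | 12% too high |
| 1.5 | 1.5 / 1.232 = 1.22 | 22% too high |
| 2 | 2 / 1.464 = 1.37 | 37% too high |

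**4. Bias against sampling error.** Bias in percentage points = (1 − c) × (prevalence at sites − prevalence elsewhere). The 95% half-width at n = 1056 is 1.96 × √(p(1 − p)/1056), with p the prevalence at the sites and simple random sampling taken for granted. The prevalences are assumed.

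| At sites | Elsewhere | National | Bias (points) | Half-width (points) |
|---|---|---|---|---|
| 5% | 4% | 4.46% | +0.54 | 1.31 |
| 5% | 3% | 3.93% | +1.07 | 1.31 |
| 5% | 2.5% | 3.66% | +1.34 | 1.31 |
| 3% | 5% | 4.07% | −1.07 | 1.03 |

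A difference of about two points between participating and other hospitals gives a bias of roughly the size of the sampling error. A one-point difference gives one well inside it.

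**The case against.** The strongest reply is that partial coverage is not a fault in itself. A probability sample of hospitals holding 46% of births could support a national estimate, and voluntary sites are normal for a registry. That is right. The 46% matters only because the hospitals chose to join; it measures how much rests on extrapolation, not how large the error is.

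The protocol also acknowledges differences between sites and plans heterogeneity statistics, meta-regression and random intercepts. These compare hospitals inside the registry and carry no information about those outside it. The quotas by province, if filled, do remove bias from differences between provinces. What remains is the difference between participating and other hospitals within a province, and the protocol gives no reason to expect that to be large.

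Three stronger readings are tempting and should not be made.
- **That the national figure will be too high.** Nothing in the protocol says that participating hospitals saw more infection; the direction is unknown.
- **That nothing links the draw to individual hospitals.** Appendix 3 stops at province, but the Design section refers the list for selection to Appendix 1, which was not in the text available for review. Numbers per hospital may be there, and whether every province has a site cannot be checked.
- **That reweighting by province is missing.** The quotas are already proportional to births, so if they are filled, weighting changes nothing beyond rounding.

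**Conclusion.** The point holds as a mismatch between the stated target and the population that can be sampled. The objective, the inclusion wording and the allocation are national; the draw is confined to self-selected sites with roughly 46% of births. The design does not by itself support a national prevalence.

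The size of the error is unknown. Over assumed ratios of 0.5 to 2 it runs from about 35% understatement to 37% overstatement, with none if participating and other hospitals have equal prevalence. This assumes that the quotas are filled and that 172,000 over 370,827 is a fair approximation to coverage. It also takes the sites in Substudy 4 to be the registry's 100 sites, as the Design section's reference to Appendix 1 indicates.

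The estimate remains useful for the hospitals that took part. What needs correcting is the population it is said to describe.

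**What to change.** 1. Restate the Substudy 4 objective, and word any conclusion drawn from it, as prevalence among eligible women delivering at the participating sites. Eligible should mean what the inclusion criteria already say: 24 weeks or more, no earlier positive laboratory test, PCR in the stated window around delivery, and consent.
2. Reconcile the Patients and Inclusion criteria text, which admits any Spanish maternity hospital, with the site list in Appendix 1.
3. Give any national figure only as an extrapolation, labelled as such, with a sensitivity range for the uncovered births that runs in both directions, for example the ratios of 0.5 to 2 used above.

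A table of site deliveries over births for each province is not a good substitute. Deliveries are counted where they occur and births where the mother lives, so the ratio is not a clean coverage share.

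The change needs wording and one short sensitivity calculation, with no new data collection. The price is a less sweeping claim.
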